#### Costs

We will consider four types of costs: (1) the costs of offering the intervention (SOS training + CAU or CAU), (2) costs stemming from general health care uptake besides SOS training + CAU or CAU, including the costs of medication, (3) patients' out-of-pocket expenses (eg traveling costs, leisure time spent on receiving care), (4) costs stemming from productivity losses due to absenteeism or reduced efficiency while at work (presenteeism). The first two types of costs are also known as the direct medical costs and these will be based on the full economic costs of offering the interventions. Here, we will use the pertinent Dutch guideline for economic evaluation [100], and rely on the standard cost prices reported therein. Productivity losses will be based on the gender- and age-specific labour costs. Data on resource use (health care uptake) and productivity losses will be collected with the widely used TiC-P [88].

#### Effects

As effect measure, the 5-level variant of the 5-dimensional EuroQol instrument (EQ-5D-5 L) [86] will be used to compute health gains expressed in quality adjusted life years (QALYs). Health utilities are a major feature of the EQ-5D instrument. As the EQ-5D-5 L is relatively recent update of the 3-level EQ-5D, studies that directly elicit preferences from general population samples to derive value sets to calculate the EQ-5D-5 L health utilities are under development in a number of countries, including the Netherlands [101]. In the interim, the EuroQol Group coordinated a study that administered both the 3-level and 5-level versions of the EQ-5D, in order to develop a “crosswalk” between the EQ-5D-3 L value sets and the new EQ-5D-5 L descriptive system, resulting in crosswalk value sets for the EQ-5D-5 L [102]. It is expected that the new utilities for the EQ-5D-5 L will be available when we will perform the calculations for the economic evaluation; otherwise we will use the crosswalk from the EuroQol Group to calculate health utilities.

#### Cost-effectiveness calculations

The economic evaluation will be conducted alongside the randomized trial, taking into account the CHEERS statement [103] and the 2015 ISPOR good research practices task force report on cost-effectiveness analysis alongside clinical trials [104]. Technically, the economic evaluation referred to as cost-effectiveness analysis in the following section will be a cost-utility analysis as health utilities are used as the effect measure.

Using the area under the curve (AUC) method, the periods between the measurement waves will be weighted by the utility of the health state in that period. This allows the computation of quality adjusted life years (QALYs) over the entire trial period. In similar vein, cumulative costs over the entire follow-up period will be obtained from the cost estimates at the various measurement waves. The cost-utility evaluation will be performed in line with suggestions by Drummond et al. (2005) [105], i.e. in agreement with the intention-to-treat principle, with missing data addressed using imputation.

The incremental cost-effectiveness ratio (ICER) will be calculated as follows: ICER = (C1-C2)/(E1-E2), where C stands for costs, E for effects, and subscripts 1 and 2 refer to the two trial arms (SOS training + CAU and CAU, respectively). Confidence intervals around the ICER will be calculated using a non-parametric bootstrap approach: 5,000 non-parametric bootstrapped samples will be extracted from the original dataset. For each of these bootstrapped samples, the incremental costs, incremental effects, and the incremental cost-effectiveness ratio (ICER) will be calculated. The resulting 5,000 ICERs will be used for further calculations and will be plotted on a cost-effectiveness plane. In addition, cost-effectiveness acceptability curves (CEACs) will be constructed. One-way sensitivity analyses directed at uncertainty in the main cost drivers will be performed to gauge the robustness of our findings. In addition, a sensitivity analysis in which a covariate-adjusted CEAC curve is constructed will be conducted using net benefit regression methods [106, 107].

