### Participants

Participants will be recruited in an addiction-psychiatry clinic and an addiction-psychiatry outpatient care facility in Amsterdam. Inclusion criteria are (1) 18 years of age or older; (2) substance dependence or substance abuse (involving alcohol and/or illegal drugs, including cannabis) according to Diagnostic and Statistical Manual of Mental Disorders-IV (DSM-IV) criteria; and (3) at least one other mental disorder on DSM-IV Axis I or II. Patients are excluded from the study if they (1) do not have sufficient understanding of the Dutch language; or (2) are not eligible for group therapy according to their case manager, due to for instance severe anti-social or psychopathic traits; (3) are not willing to provide informed consent. Based on a priori power analysis, we aim to include 250 (2x125) participants in this study.

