### Other variables of interest

#### General patient characteristics

General demographic characteristics such as age, gender, marital status and educational level will be collected at baseline. Furthermore, current DSM-IV diagnosis, total days of hospitalisation, all-cause mortality, Global Assessment of Functioning (GAF) and mental healthcare received by participants will be extracted from the electronic patient record.

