### Data analysis

#### Sample size calculation

A priori sample size calculations were performed using G*power 3.1.9.2. We are the first to explore effects of an intervention to reduce victimization in this target group, which makes it impossible to provide an exact estimate of effect size for the main outcome measure in this sample. In order to be able to detect a 20 % difference in treatment response between the two trial arms (50 % treatment response in SOS training + CAU versus 30 % treatment response in CAU) with α = .05 and power = .80, the total sample size should be at least 186 (N CAU + SOS training = 93, N CAU = 93). Since a drop-out of 25 % can be expected in this target group we aim to include 250 participants.

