#### Effectiveness

Primary data analyses will be performed in accordance with the intention-to-treat paradigm. In addition, per protocol analyses will be conducted. Missing data will be addressed using multiple imputation. Statistical significance will be set at α < .05, based on two-sided tests. The effect of treatment in terms of the primary and secondary outcome variables will be analysed with generalized linear mixed model regression analysis (GLMM) with adequate link functions, taking into account distributional characteristics of the data.

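### The base-case QALY difference is not adjusted for baseline EQ-5D-5L utility, although that utility is collected; adjustment appears only in a sensitivity analysis

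*Protocol article*

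**What the plan says.** All references are to the protocol article.

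- **Cost-effectiveness calculations, QALYs.** The area-under-the-curve method is used over the whole trial: "the periods between the measurement waves will be weighted by the utility of the health state in that period".
- **Same section, estimator.** The ICER is the difference in costs divided by the difference in effects between the two arms. It is recalculated in 5,000 bootstrap samples, which supply the interval and the plane. No covariate enters.
- **Same section, adjustment.** The only covariate adjustment in the economic evaluation is this: "a sensitivity analysis in which a covariate-adjusted CEAC curve is constructed will be conducted using net benefit regression methods".
- **Table 1.** EQ-5D is given at T0, T1, T2 and T3. The cost questionnaire (TiC-P) is given at T1, T2 and T3 only.
- **Randomization and treatment allocation.** The strata are treatment centre (clinic or outpatient care) and victimization in the year before baseline.
- **General patient characteristics.** Days in hospital and "mental healthcare received by participants will be extracted from the electronic patient record". No time window before T0 is stated.
- **Effectiveness.** Mixed models are planned for the primary and secondary outcomes. They are not linked to the QALY or ICER calculation.

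**The concern.** T0 utility is measured before randomization, so no T0 difference between arms can be a treatment effect. Yet it affects the QALY difference in two ways: T0 is one of the points under the curve, and a person's T0 utility is likely to predict the later utilities. The randomization is not stratified by utility, so some imbalance will remain by chance.

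An estimator that ignores T0 utility is less precise than it could be, and in the one trial that is run it is pulled toward the arm that started better. Two results, adjusted and unadjusted, are already planned. By calling the adjusted one a sensitivity analysis, the article makes the less precise one the headline. The adjusted acceptability curve leaves the ICER, its interval and the plane as they were. At stake is the third research question, on costs and effects. The primary victimization outcome is not affected.

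**Working it through.** **The plan's own figure.** The article states no precision target for QALYs or costs. The per-arm number used below comes from the primary-outcome calculation, so that is checked first. The inputs are "50 % treatment response in SOS training + CAU versus 30 % treatment response in CAU", with the result "with α = .05 and power = .80, the total sample size should be at least 186", two-sided. With a mean proportion of 0.40:

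n per arm = [1.960 × √(2 × 0.40 × 0.60) + 0.842 × √(0.50 × 0.50 + 0.30 × 0.70)]² / 0.20² = (1.358 + 0.571)² / 0.04 ≈ 93, total 186.

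Allowing for 25% drop-out, 186 / 0.75 = 248, in line with the 250 planned. Hence 125 per arm ("we aim to include 250 (2x125) participants in this study").

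**Assumed inputs (not in the article).** Utility SD 0.20 to 0.30, equal at all waves; one common correlation ρ of 0.4 to 0.7 between any two waves; complete data on 125 per arm; utility interpolated linearly between waves.

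**Step 1, weights.** For waves at 0, 2, 8 and 14 months the trapezoid weights are 1, 4, 6 and 3 months, or (1, 4, 6, 3)/12 years, 14/12 years in all. T0 itself carries 1/12 QALY per unit of utility, which is 1/14 = 7.1% of the total weight.

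**Step 2, slope of QALY on T0 utility.** (1 + 13ρ)/12.
- ρ = 0.4: 6.2/12 = 0.52
- ρ = 0.7: 10.1/12 = 0.84

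**Step 3, chance imbalance at T0.** One standard error is SD × √(2/125) = SD × 0.1265.
- SD 0.20: 0.025
- SD 0.30: 0.038

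**Step 4, shift in the QALY difference from a one-standard-error imbalance.**
- ρ = 0.4, SD 0.20: 0.0253 × 0.517 = 0.013
- ρ = 0.7, SD 0.30: 0.0379 × 0.842 = 0.032

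**Step 5, standard error of the unadjusted QALY difference.** The sum of squared weights is 62/144 = 0.431, and the square of their sum is 196/144 = 1.361. The QALY variance is SD² × [(1 − ρ) × 0.431 + ρ × 1.361].
- ρ = 0.4: factor 0.803; at SD 0.20 the standard error is 0.20 × √0.803 × 0.1265 = 0.023
- ρ = 0.7: factor 1.082; at SD 0.30 the standard error is 0.30 × √1.082 × 0.1265 = 0.039

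**Step 6, share of variance due to T0 utility.** Slope² divided by the factor in step 5.
- ρ = 0.4: 0.517²/0.803 = 0.33
- ρ = 0.7: 0.842²/1.082 = 0.65

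This share is the proportion of variance that adjustment removes. Its square root, 0.58 to 0.81, is the shift in step 4 as a fraction of the standard error in step 5. Neither depends on the SD or on the number per arm, only on ρ. With a weaker correlation of 0.3 the share is 0.235.

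**Direct and indirect parts.** Of the shift in step 4, the direct part is 0.025/12 to 0.038/12, or 0.002 to 0.003 QALY. The rest comes through the correlation of T0 with the later waves.

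**The case against.** **The unadjusted comparison is valid.** Under randomization it is unbiased on average, and the bootstrap already carries baseline variation into the interval, the plane and the acceptability curve. This stands. What remains is lost precision, and bias conditional on the imbalance that actually occurs.

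**Adjustment is already planned.** Net benefit regression is named, and an article may leave the covariate list to the full plan. This stands too: the unnamed covariates are not themselves the fault. But the ranking of the two analyses is fixed in the article, and the adjusted curve does not alter the base-case ICER or its interval.

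**The size rests on assumptions.** The article gives neither SD nor correlation, and a correlation that does not fade over 14 months may be generous. Centre or prior victimization, if related to utility, would also make T0 imbalance smaller than under simple randomization. The ranges must be read with that in mind.

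**Stronger readings that the documents do not support.**
- A reader might infer that a T0 imbalance enters the QALY difference one for one. It does not: the slope is 0.52 to 0.84, and only 1/12 of a QALY per unit is direct.
- A reader might infer that the shift matches the standard error. Under this model it is always smaller, being the square root of the variance share.
- A reader might infer the same fault for costs because TiC-P is not given at T0. A comparison of cumulative follow-up costs does not require a baseline cost, stratification by clinic or outpatient care partly balances care use, and nothing in the article allows a size to be put on any cost imbalance.
- A reader might convert the shift into euros or say that it decides the conclusion. The article states no value per QALY and no expected QALY gain, so neither can be shown.

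**Conclusion.** The point holds for the QALY side. The article makes the unadjusted QALY difference the base case while collecting, before randomization, the one covariate most closely tied to it. This costs precision and leaves the result open to chance imbalance; it does not make the analysis invalid.

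Under the stated assumptions, an imbalance of one standard error moves the estimate by rather more than half to about four fifths of its own standard error, and between a third and two thirds of the variance could be removed. Confidence is high on what the article fixes and moderate on the size, which depends on the assumed correlation. On costs there is no comparable finding.

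**What to change.** In the section on cost-effectiveness calculations, exchange the two analyses:

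1. Within each bootstrap sample, estimate the incremental QALY from a regression of QALYs on arm, T0 EQ-5D-5L utility and the two randomization strata.
2. In the same sample, estimate the incremental cost from a regression of costs on arm and the strata.
3. Use these estimates for the base-case ICER, its interval, the plane and the acceptability curve.
4. Report the unadjusted result as the sensitivity analysis.

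The wording should be settled before the data are analysed by arm, so that the choice between the two results is not made afterwards.

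This is a change of analysis text only: T0 utility and the strata are already recorded, and no visit, instrument or patient is added. Adjusting costs for hospital days and mental health care before T0 is at most an optional addition. It would need a stated pre-T0 window for the record extraction, and it would be partial, since those records do not cover out-of-pocket or productivity costs.

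### The planned confidence interval on the ICER, formed from 5,000 bootstrapped ratios, is unreliable if the QALY difference is small, and the plan has no rule for that case

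*Protocol article*

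**What the plan says.** All of this is in the protocol article under Cost-effectiveness calculations. The estimand is a ratio: "ICER = (C1-C2)/(E1-E2), where C stands for costs, E for effects". The effect measure is the QALY, derived from the EQ-5D-5L (section Effects).

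For uncertainty, "Confidence intervals around the ICER will be calculated using a non-parametric bootstrap approach", and "5,000 non-parametric bootstrapped samples will be extracted from the original dataset". Incremental costs, incremental effects and the ICER are computed in each sample. Then: "The resulting 5,000 ICERs will be used for further calculations and will be plotted on a cost-effectiveness plane".

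Two further displays are planned. "In addition, cost-effectiveness acceptability curves (CEACs) will be constructed". Net benefit appears once, as "a sensitivity analysis in which a covariate-adjusted CEAC curve is constructed will be conducted using net benefit regression methods".

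The only confidence interval named for the economic evaluation is the one on the ratio. The section does not say what happens to it if the QALY difference is near zero or changes sign across replicates.

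**The concern.** A ratio is a poor quantity to order when its denominator can change sign.

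- A negative ICER arises when SOS training is cheaper and better (dominant) and also when it is dearer and worse (dominated).
- A positive ICER arises when it is dearer and better (north-east quadrant) and also when it is cheaper and worse (south-west quadrant).
- As the QALY difference approaches zero, the ratio grows without limit in either direction.

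Sorting such values does not sort replicates from favourable to unfavourable, so limits read from the sorted list have no clear meaning.

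A small QALY difference is plausible here. Follow-up is 14 months, the intervention is a 12-session group training added to ongoing care, and the sample was sized on victimization response. At stake is the interval that would accompany the answer to the third research question, on costs and effects, and any probability obtained by counting ratios against a threshold.

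**Working it through.** **The plan's own design figure.** The section Sample size calculation gives 186 for 50% versus 30% response, two-sided alpha 0.05, power 0.80. Per arm: [1.96·√(2·0.4·0.6) + 0.8416·√(0.5·0.5 + 0.3·0.7)]² / 0.2² = (1.358 + 0.571)² / 0.04 ≈ 93, so 186 in total. For 25% drop-out, 186 / 0.75 = 248, rounded to 250. This reproduces, but it says nothing about precision for QALYs or costs.

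**Inputs.** From the documents: 125 per arm, 14 months, 5,000 replicates. Assumed, because the documents give none: QALY SD 0.20 to 0.25, cost difference EUR 500 with SE 1,500, no correlation, approximately normal replicates, threshold EUR 50,000 per QALY.

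**Standard error of the QALY difference.** SE = SD·√(2/125): 0.20 × 0.1265 = 0.025; 0.25 × 0.1265 = 0.032.

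**Share of replicates with a negative QALY difference**, Φ(-difference/SE):

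| QALY difference | SE 0.025 | SE 0.0316 |
|---|---|---|
| 0.02 | Φ(-0.80) = 21% | Φ(-0.63) = 26% |
| 0.05 | Φ(-2.00) = 2.3% | Φ(-1.58) = 5.7% |
| 0.10 | Φ(-4.00) ≈ 0 | Φ(-3.16) < 0.1% |

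For scale, over 14 months a difference of 0.02 QALY is a mean utility difference of 0.02 × 12/14 = 0.017; 0.10 QALY is 0.086.

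**Quadrants at 0.02 QALY (SE 0.025).** P(cost difference < 0) = Φ(-500/1,500) = 37%.
- Dominant: 0.79 × 0.37 = 29%.
- Dominated: 0.21 × 0.63 = 13%.
- North-east: 0.79 × 0.63 = 50%.
- South-west: 0.21 × 0.37 = 8%.

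So 42% of the ratios are negative, and about a third of those (13/42) are the worst outcome, not the best.

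**Interval from the ordered ratios.** By simulation, the 2.5th and 97.5th percentiles are about -565,000 and +604,000 EUR per QALY, around a point estimate of 500 / 0.02 = 25,000.

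**Net benefit from the same replicates.** INMB = 50,000 × 0.02 - 500 = 500. SE = √[(50,000 × 0.025)² + 1,500²] = √3,812,500 = 1,953. The 95% interval is 500 ± 1.96 × 1,953, about -3,327 to 4,327: finite and ordered. P(INMB > 0) = Φ(500/1,953) = 60%.

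**Counting ratios instead.** When the QALY difference is negative, a ratio below the threshold means a negative net benefit, so those replicates are judged the wrong way round. By simulation the count gives 72%, against the correct 60%.

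**Coverage.** This was a separate simulation of 1,000 trials per scenario, with assumed QALY SD 0.20, cost SD EUR 15,000 and cost differences from EUR -1,000 to 8,000. At true differences of 0.005 to 0.02 QALY, the nominal 95% percentile interval covered between 0.82 and 0.99. Fieller's interval covered 0.94 to 0.96 but was unbounded in 87% to 95% of those trials, so a bounded interval on the ratio cannot be right there. At 0.10 QALY the percentile interval covered 0.95 to 0.96.

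**The case against.** The strongest reply is that the plan already holds most of the remedy. It computes incremental costs and effects in every replicate, plots a cost-effectiveness plane, builds acceptability curves and includes net benefit regression. A reader might infer from the ratio problem that the economic evaluation cannot tell a dominant from a dominated strategy. The documents do not support that: the plane separates the four quadrants. Since a plane has cost and effect axes, the ICERs plotted on it can only be cost-effect pairs, so the wording there is partly shorthand. This part of the reply stands and limits the fault to the ICER interval and to calculations made on the ratios.

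Second, the percentile method is not named; it is inferred from an interval based on bootstrapped ICERs. That is correct, and the text should be read as not excluding naive ordering, not as prescribing it. But no bounded interval from ordered ratios avoids the difficulty, so naming another such method would not cure it.

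Third, the illustration uses a small effect. That also stands: at 0.10 QALY the interval behaves well, so it would be wrong to call it invalid in general.

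A reader might also take "with missing data addressed using imputation" as a sign of single imputation before resampling. The documents do not support this. The sections Effectiveness and Discussion both state multiple imputation, and nothing says single. How imputation and bootstrap are combined is ordinarily left to the analysis plan.

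**Conclusion.** The point holds, conditionally. The article commits to a confidence interval on a ratio and gives no rule for a denominator near or across zero. If the QALY difference is around 0.02 or less, that interval is unreliable and uninterpretable; its coverage can be too high or too low. At 0.05 QALY about 2% of replicates are negative (SE 0.025), and at 0.10 the difficulty is gone. Every figure for the economic evaluation here rests on assumed standard deviations and differences. The consequence is a misleading secondary interval, and possibly a miscounted probability (72% against 60% in the example), not an invalid economic evaluation. It is worth correcting because the correction is nearly free.

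**What to change.** Using the same 5,000 pairs of incremental cost and incremental QALY:

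- Report bootstrap intervals for incremental costs, incremental QALYs and incremental net monetary benefit at stated willingness-to-pay values.
- State that the acceptability curve is built from net benefit, not from counts of ratios below a threshold.
- Give an interval on the ICER only if essentially no replicates cross a zero QALY difference. Otherwise give the ICER as a point estimate with the percentage of replicates in each quadrant.

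The cost is a few sentences of wording and minor computing. No new data or extra resampling are needed, and net benefit methods are already in the plan.

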## Ethical approval

This RCT has been reviewed and approved by the ethics committee of the Academic Medical Center of the University of Amsterdam, Amsterdam, The Netherlands and will be conducted in accordance with the Declaration of Helsinki [108].

## Discussion

Patients with comorbid mental and substance use disorders are vulnerable to victimization [1–5]. There is a strong need for interventions that reduce victimization of patients [2–4, 37, 53]. This randomized clinical trial is the first to test the effectiveness of an intervention that aims to reduce vulnerability for victimization in patients with dual diagnosis. We will test whether adding the Self-wise, Other-wise, Streetwise (SOS) training to care as usual results in a reduction of victimization. Besides, we will examine improvement on secondary outcome measures and cost-effectiveness.

Previous studies testing the effectiveness of psychosocial interventions in similar target groups have been hampered by small samples, poor experimental design, short follow-up periods and high loss to treatment and loss to follow-up [40]. Major strengths of this study are the follow-up period of 14 months, the relatively large sample size of 250 individuals and the large battery of validated and clinically relevant outcome measures. Furthermore, those assessing outcomes will be blind to treatment allocation. Our main challenges in this study are expected to be treatment adherence and preventing drop-out. We will work closely together with patients’ mental health care professionals to prevent drop-out as much as possible. Moreover, participants will receive monetary compensation for completing follow-up assessments. Finally, missing data will be addressed using multiple imputation.

If SOS training is effective in reducing vulnerability for victimization it can be implemented in mental health care and contribute to the safety and well-being of patients.
